### Validation of the Study Procedure

Each patient enrolled in the validation study will have his or her level of consciousness assessed at baseline with a single administration of the CRS-R. Next, the level of consciousness and swallowing abilities will be assessed with three tools during three separate sessions (only one administration of the FOTT-SAS) in the morning or the afternoon in order to assess the tool's intrarater and interrater reliability. The baseline assessment and sessions will be spread over 5 consecutive days.

CRS-R: This is a standardized neurobehavioral assessment of consciousness composed of six subscales (auditory, visual, motor, oromotor/verbal, communication, and arousal). It assesses different functions with various numbers of hierarchically arranged items that distinguish UWS, MCS, and EMCS patients. The total score is composed of the sum of the maximum scores obtained in each subscale.SECONDs: It is shorter to administer (median of 7 min) and requires only a mirror as material. It consists of eight items: observation and reporting of spontaneous behaviors, response to command, communication, visual pursuit and fixation, pain localization, oriented behaviors, and arousal. We have chosen this consciousness tool during sessions rather than the CRS-R because of its short duration so that the SWADOC can be administered immediately before or after, given that attentional abilities are often reduced in patients with DOC. The SECONDs provides a total score directly reflecting one diagnosis (0 = coma; 1 = UWS; 2–5 = MCS–; 6–7 = MCS+; 8 = EMCS).SWADOC: This tool includes a battery of 56 quantitative and qualitative items. Quantitative items are grouped in the SWADOC-scored, with oral and pharyngeal subscores and a total score. Running the whole SWADOC lasts between 15 and 25 min based on preliminary tests.FOTT-SAS: The results of the SWADOC-scored in one session will be compared to those of the FOTT Swallowing Assessment of Saliva (FOTT-SAS) (30). The test comprises seven questions; if items 1–4 are answered “Yes” and items 5–7 are answered “No,” oral intake should be initiated (Supplementary Material 4). The FOTT-SAS includes items that can be scored based on the administration of the SWADOC. In that respect, no additional administration will be required.

The clinical protocol procedure is illustrated in Figure 3.

**Figure 3 F3:**
[figure not shown]
Study protocol. Example of the assessment program for a patient. The program for each patient is organized such that the three sessions take place over 5 days in the morning or in the afternoon. The SECONDs is administered before or after the SWADOC. Examiner 2 will administer the SWADOC before or after examiner 1 in one of the three sessions. Examiner 1 will score the FOTT-SAS after one of the three sessions. SECONDs, Simplified Evaluation of CONsciousness Disorders; SWADOC, SWallowing Assessment in Disorders Of Consciousness; FOTT-SAS, Facial Oral Tract Therapy Swallowing Assessment of Saliva.

Because of clinical realities, no attempt will be made beforehand to standardize the order (SECONDs before or after SWADOC and examiner 2 before or after examiner 1) or time of day (morning or afternoon) of evaluations. However, during data collection, efforts will progressively be made to balance the order and time of day and the time of evaluation of examiner 2 (before or after examiner 1).

The administration of the SWADOC at each session will allow us to assess the tool's intrarater reliability (temporal stability). Directly before or after one of the three sessions, a second examiner will administer the SWADOC a second time to test its interrater reliability. The second assessment will be blinded to the results of the first. To be able to take into account potential mismatches between the ratings of the two examiners, each scoring protocol will be analyzed directly after the interrater session and a discussion will follow to try to understand the reasons for any discrepancies. This information will be noted in the protocol. After the recruitment procedure and depending on the degree of agreement based on the statistical analysis, modifications of the instructions, and/or items will be considered based on the qualitative information collected from the examiners.

Sensitivity to change will determine whether changes in the level of consciousness (variations in SECONDs scores) result in changes in the SWADOC-scored across the three assessments of the same patient. Repeating the SECONDs assessment will also allow for a reliable assessment of the patient's level of consciousness (UWS, MCS–, MCS+, or EMCS) and decrease the risk of misdiagnosis (31).

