#### Validity

##### Concurrent Validity

The results of the SWADOC-scored will be compared to the FOTT-SAS score for the same time and with the best score using Pearson's correlation (parametric test) or Kendall's correlations (nonparametric test) after examination of the data distributions.

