### Limitations and Pitfalls

There are a number of limitations on this study especially because of the clinical challenges of dealing with patients with DOC. The main limitation is the feasibility of having each patient undergo a baseline administration of the CRS-R and three assessments. This group's arousal fluctuates considerably, as they are highly sensitive to stress and fatigue, and often subject to medical complications (e.g., vomiting, pain, respiratory infections, etc.) that may limit their availability to participate in the study. To take into account this pitfall of the application of the methodology to patients with DOC, we chose to extend the evaluation period to five days rather than two days as initially planned.

Although, we have developed the most accurate levels possible for each item and a complete scoring guide, the SWADOC is based on subjective observations of swallowing components. The interrater reliability will help us determine the consistency of the rating system between examiners. Depending on these results, the scale may be adapted.

Furthermore, the decision to assess the level of consciousness using the SECONDs may seem questionable because this scale is recent, but it is derived from the CRS-R, which is known to be the gold standard scale for behavioral assessment of consciousness. Nevertheless, the SECONDs is much quicker to administer and includes the five CRS-R items that detect 99% of MCS patients (12). Moreover, this scale has good intra- and inter-rater reliability (kappas ranging from 0.85 to 0.91 and 0.82 to 0.85, respectively). However, we considered adding one administration of the CRS-R at baseline before the three sessions because the CRS-R gives more details and precision on the patient's overall state, including reflexes.

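### The FOTT-SAS is scored at one of three sessions though it needs no extra administration, so the best-score comparison can cross occasions; separately, sensitivity to change is anchored on consciousness alone

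*Protocol article*

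**What the plan says.** The SWADOC is administered at each of three sessions within five consecutive days. The FOTT-SAS is not. Validation of the Study Procedure specifies "only one administration of the FOTT-SAS", and the Figure 3 legend agrees: "Examiner 1 will score the FOTT-SAS after one of the three sessions". The reason is not patient burden, because the same section says: "The FOTT-SAS includes items that can be scored based on the administration of the SWADOC". It continues: "In that respect, no additional administration will be required".

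Under Concurrent Validity, the SWADOC-scored results are to be "compared to the FOTT-SAS score for the same time and with the best score". The article does not define the best score.

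The text after Figure 3 sets the criterion for responsiveness: "Sensitivity to change will determine whether changes in the level of consciousness (variations in SECONDs scores) result in changes in the SWADOC-scored", over a patient's three assessments. No repeated swallowing reference is planned. Study Hypotheses lists the relation between SWADOC scores and level of consciousness as the second hypothesis, still to be tested.

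**The concern.** There are two separate issues.

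**Occasion mismatch.** Only the SWADOC is repeated, so the best score most naturally means the highest of a patient's SWADOC scores. Set against a single FOTT-SAS, it will often pair two different days. Limitations and Pitfalls says that arousal in these patients varies a good deal. A low best-score coefficient could therefore reflect day-to-day variation rather than poor validity. The plan also gives up two reference scores per patient that it says need no additional administration.

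**Choice of anchor.** The SECONDs measures consciousness, not swallowing. Using it as the sole criterion for sensitivity to change assumes that swallowing moves with consciousness, which is the second hypothesis. If SWADOC scores do not follow SECONDs scores, the result has two explanations that the design cannot tell apart: the tool misses change, or swallowing does not track consciousness.

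**Working it through.** **The plan's own figure.** The article's only computed figure is the sample size. With four groups, alpha 0.05 and eta-squared 0.1, f = √(0.1/0.9) = 0.333. At N = 104 the noncentrality is 104 × 0.1/0.9 = 11.56 and power is 0.808, so 104 reproduces. Nothing below depends on it.

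**Inputs from the article.** Three SWADOC sessions; one FOTT-SAS; examiner 1 scores the FOTT-SAS from a SWADOC administration; SECONDs score 0 to 8.

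**Inputs assumed.** Between-session stability and the reliability of each scale, since the article gives neither.

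**Step 1: how often the occasions differ.** If sessions are exchangeable and scores are untied, the best of three falls in the FOTT-SAS session with probability 1/3 and elsewhere with probability 2/3. Counting ties on the 0–24 scale, the FOTT-SAS session holds a best score in about 37–38% of patients.

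**Step 2: effect on the correlation.** Model each score as trait + session deviation + error. Trait variance is s (the stability), session variance is 1 − s, and error variance is 0.25, independent between scales. The same-session correlation is then 1/(1 + 0.25) = 0.80. Simulation of 400,000 patients gives:

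| Stability s | Same session | Best SWADOC vs one FOTT-SAS | Best vs best |
|---|---|---|---|
| 0.5 | 0.80 | 0.62 | 0.80 |
| 0.6 | 0.80 | 0.67 | 0.81 |
| 0.7 | 0.80 | 0.71 | 0.83 |
| 0.8 | 0.80 | 0.76 | 0.84 |
| 0.9 | 0.80 | 0.80 | 0.86 |
| 0.95 | 0.80 | 0.82 | 0.87 |

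The loss against the same-session value runs from 0.18 at s = 0.5 to 0.04 at s = 0.8. It vanishes near 0.9 and reverses at 0.95. For s = 0.5 to 0.8, rounding to a 0–24 and a 0–7 scale changes little: 0.61–0.74 for best against one, and 0.77–0.82 for best against best.

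**Step 3: would FOTT-SAS change be an independent anchor?** In the same model the correlation between the two change scores is (1 − s + shared error)/(1 − s + 0.25). At s = 0.8 with no shared error this is 0.20/0.45 = 0.44. If 70% of the error variance is shared (assumed, because one examiner scores both from one administration), it is (0.20 + 0.175)/0.45 = 0.83. The tool is no better in the second case, so agreement between the two changes would partly show shared observation.

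**Step 4: the SECONDs anchor.** No arithmetic is needed. The sensitivity-to-change definition takes SECONDs variation as the sole criterion, while Study Hypotheses treats the link between SWADOC scores and consciousness as a question for the study. A positive result would support both the link and responsiveness. A null result would identify neither failure.

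**The case against.** The strongest reply is that the article is consistent and its main comparison is correctly paired. It states one FOTT-SAS throughout, and the same-time correlation does not cross occasions. That stands: this is a design weakness in an additional analysis, not a contradiction. A reader might infer that concurrent validity as a whole is compromised by the single FOTT-SAS; the documents do not support that.

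Second, the attenuation depends on an assumed stability. Patients are medically stable, at least 28 days after injury, and seen within five days, so stability could be 0.9 or more and the loss nil. That also stands, and the size is therefore conditional. The crossing of occasions is not, given the natural reading of the best score.

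Third, the SECONDs anchor does not follow from scoring the FOTT-SAS once. The article chose it directly, and three FOTT-SAS scores would leave the definition unchanged. This is correct, and the two issues are kept apart here. A single FOTT-SAS does rule out any change score on a swallowing reference. A reader might then infer that repeated FOTT-SAS scores would supply a proper anchor; Step 3 shows why they would not.

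Fourth, a reader might infer from the SECONDs intrarater kappas in Limitations and Pitfalls (0.85 to 0.91) that very few patients will change. With four equal groups and unweighted kappas on diagnosis, agreement is 0.25 + 0.75κ. Discordance is then 11.3% to 6.8%, or about 12 to 7 of 104 patients per pair of sessions. That does not measure the information available. The plan uses variations in SECONDs scores, and scores 2–5 share one diagnosis, as do 6–7. The article also does not say what kind of kappa these are.

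Finally, tracking change and monitoring therapy are listed as objectives of the tool. The article does not say that the five-day window will demonstrate responsiveness to therapy, and should not be read as claiming it.

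**Conclusion.** The point holds as a cheap improvement. The plan forgoes two reference scores per patient that, by its own account, need no further administration. As a result its best-score comparison will often pair different sessions: up to about two thirds of patients if sessions are exchangeable and untied. Whether this matters numerically depends on a stability that the documents do not give. At 0.5 to 0.8 the correlation falls from 0.80 to between 0.62 and 0.76; at about 0.9 there is no loss. These values also assume independent errors, which is doubtful when one examiner scores both scales from one administration.

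Independently of any number, the SECONDs-anchored analysis cannot by itself establish or refute sensitivity to swallowing change, because it takes the second hypothesis as given. It remains a useful analysis of that hypothesis.

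**What to change.** - Have examiner 1 score the FOTT-SAS after each of the three SWADOC sessions.
- Keep the same-session comparison as the main concurrent-validity analysis. Use all three pairs per patient and account for within-patient clustering.
- Define the best score, and run that version as best SWADOC against best FOTT-SAS, labelled secondary.
- Label the SECONDs analysis as a within-patient association of SWADOC with level of consciousness, place it under the second hypothesis, and draw no conclusion on responsiveness to swallowing change from it alone.
- Report within-patient FOTT-SAS change, if at all, as descriptive support. State that it comes from the same examiner and the same administration and so is not an independent anchor.

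The cost is two more completions of a seven-question form per patient, from sessions already scheduled and without further patient contact, plus changes to the analysis wording. The responsiveness statement becomes narrower. Sessions already completed without a FOTT-SAS score stay missing, so the change is worth making early. The sample size is unaffected.

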#### Reliability

The intrarater (i.e., SWADOC-scored vs. SWADOC-scored by the same examiner on the same day and on two different days) and interrater reliability (i.e., SWADOC-scored vs. SWADOC-scored on the same day by two different examiners) will be calculated in two separate analyses using weighted Fleiss's kappa coefficients (K_W_). A value below 0 will be considered to indicate poor agreement, between 0 and 0.2 slight agreement, between 0.21 and 0.4 fair agreement, between 0.41 and 0.6 moderate agreement, between 0.61 and 0.8 substantial agreement, and between 0.81 and 1 almost perfect to perfect agreement (32). We will also determine the internal consistency of the SWADOC-scored with Cronbach and Spearman intercorrelations to determine the interrelatedness of the constituent items.

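### Rater blinding is stated only for the examiner pair, and a scheduled score discussion can fall between examiner 1's repeat ratings, so the intrarater ratings are not protected as independent

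*Protocol article*

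**What the plan says.** All references are to the protocol article.

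- **Timing** (Validation of the Study Procedure): "The baseline assessment and sessions will be spread over 5 consecutive days". SWADOC is given at each of the three sessions, and these repeats supply the intrarater (temporal stability) data.
- **Intrarater comparison** (Reliability): SWADOC-scored against SWADOC-scored "by the same examiner on the same day and on two different days". The same-day part implies two sessions by examiner 1 on one day.
- **Interrater procedure** (Validation of the Study Procedure, text after Figure 3): "Directly before or after one of the three sessions, a second examiner will administer the SWADOC a second time to test its interrater reliability". The next sentence is the blinding statement: "The second assessment will be blinded to the results of the first".
- **Position of the interrater session** (Figure 3 legend): "Examiner 2 will administer the SWADOC before or after examiner 1 in one of the three sessions". The article does not say which of the three.
- **Score review** (same section): "each scoring protocol will be analyzed directly after the interrater session and a discussion will follow to try to understand the reasons for any discrepancies".
- **Other blinding** (Relationship Between Swallowing Components and Levels of Consciousness): the analyst is blind to consciousness category. This does not concern the raters.

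**The concern.** A test–retest kappa measures the stability of the tool only if the second rating is made without using the first. The plan recognises this for the two examiners and states blinding for them. For its other reliability analysis, in which one person scores the same patient three times within days, it states no equivalent safeguard. It also schedules a step in which scores are examined and discrepancies talked through, possibly while examiner 1 still has intrarater sessions to complete.

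Reliability is part of the main hypothesis (Study Hypotheses). Each of the eight scored items has four levels, and Limitations and Pitfalls concedes that the ratings rest on subjective observation. An examiner who hesitates between two levels could settle the matter by repeating the earlier one. The intrarater kappa would then partly describe recall or copying. The Reliability section reads kappa in verbal bands, so a modest shift could change the published label. Contamination of this kind is hard to identify once the ratings exist, so the safeguard belongs in data collection.

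**Working it through.** **1. Scope of the blinding sentence.** It stands between the sentence introducing the second examiner and the one on mismatches between the two examiners' ratings. Its natural scope is that pair. No other sentence limits examiner 1's access to his or her own earlier sheets.

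**2. What the discussion does to the three sessions.** Examiner 1's sessions give three pairs: (1,2), (1,3) and (2,3). The discussion follows the interrater session immediately. The text does not name the participants, but the two examiners are the obvious ones.

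| Interrater session | Pairs completed before the discussion | Pairs with a rating after it |
|---|---|---|
| 1 | none | 3 |
| 2 | (1,2) | 2 |
| 3 | all three | 0 |

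If the interrater session were spread equally over the three positions (an assumption; the article does not fix this), (0 + 1 + 3)/9 = 4/9, or about 44% of pairs, would be complete before any discussion. The other 5/9 would contain at least one rating made after it.

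**3. Effect of copying on kappa.** The plan gives no expected or target intrarater kappa, so there is no figure of its own to reproduce on this point. Its only computed figure, 104 patients for the ANOVA, is unaffected.

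Weighted kappa is k = 1 − Do/De, where Do is observed and De is chance-expected weighted disagreement. If a random share m of second ratings repeats the first and the marginal distributions are unchanged, Do becomes (1 − m)Do and De stays the same. So

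k_obs = 1 − (1 − m)(1 − k) = k + m(1 − k).

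Taking k = 0.55 (assumed) and m = 10–30% (assumed, no source in the document):

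- m = 0.10: 0.55 + 0.10 × 0.45 = 0.595
- m = 0.20: 0.55 + 0.20 × 0.45 = 0.640
- m = 0.30: 0.55 + 0.30 × 0.45 = 0.685

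The plan's moderate band is 0.41–0.60 and its substantial band starts at 0.61. From 0.55, reaching 0.61 needs m = (0.61 − 0.55)/0.45 = 0.133. The label changes at 20% and 30%, but not at 10%.

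**4. Check by simulation.** For a four-level item with latent correlation 0.7 between two ratings (assumed) and 400,000 pairs, linear-weighted kappa was 0.479 without copying and 0.531, 0.609 and 0.740 with 10%, 25% and 50% copying. The formula gives 0.479 + 0.10 × 0.521 = 0.531, 0.479 + 0.25 × 0.521 = 0.609, and 0.479 + 0.50 × 0.521 = 0.740. The two agree.

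**5. What the formula leaves out.** It covers copying only, for one pair of ratings. It does not cover a change in scoring habit after the discussion, which can raise or lower agreement with earlier sessions, or real change in the patient, which lowers it.

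**The case against.** **This is silence in a condensed article.** Custody of score sheets is the kind of detail a journal article leaves to the full protocol or to the administration guide, neither of which is shown. The article never says that examiner 1 has the earlier scores to hand. This stands as a limit: a reader might infer that earlier sheets will be available, and the document does not support that. It only fails to exclude it. The objection does not dispose of the point, because the article states rater blinding for one reliability analysis and not the other, and because the discussion of scores during the series is written procedure.

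**The blinding sentence could be read as covering any later assessment.** Its position makes this unlikely. Even on that reading, a discussion held before later sessions would undo it.

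**The direction of the bias is not fixed.** This stands. A reader might infer that intrarater kappa must come out too high. Each session is a fresh bedside administration in patients whose arousal varies, and true change lowers kappa. The discussion could also shift later scoring away from earlier scoring. Only the copying and recall component has a known direction.

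**The numbers are illustrative.** This stands. The copying share and the starting kappa are assumed, 0.55 lies near a band edge, the lowest case keeps its label, and the bands are descriptive with no pass/fail rule attached. The plan also cites precise level definitions and a full scoring guide, which should limit guesswork.

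**Memory cannot be blinded.** This is true of every same-rater design over a few days. What can be remedied is access to sheets and the timing of the discussion.

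**Conclusion.** The point holds in a limited form. The stated blinding covers the examiner pair, and the intrarater ratings have no stated protection. Following the text as written can put a review of scores before later intrarater ratings whenever the interrater session is the first or second. Later ratings are then not independent of earlier ones.

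The size cannot be derived from the document. The shift from 0.55 to between 0.595 and 0.685 rests on an assumed 10–30% of copied ratings, a random share and unchanged marginals. It shows that a change of label is possible, not that one will occur. The document does not support saying that intrarater reliability will be overstated overall, or that examiners will work from their earlier sheets. Sample size and the choice of kappa are unaffected. The change is worth making because it is cheap and protects an estimate on which the main hypothesis rests.

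**What to change.** In Validation of the Study Procedure:

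1. State that each SWADOC-scored sheet is completed and sealed, or locked in the database, at the end of the session, and is not available to examiner 1 until that patient's last session.
2. Move the discrepancy discussion to after the patient's last session. Without this, item 1 would conflict with the existing text. If the discussion stays where it is, report intrarater kappa separately for session pairs completed before it. That is the weaker option: patients whose interrater session comes first contribute no such pair.
3. Because examiner 2 may go first, reword the blinding sentence so that each examiner is blind to the other's ratings.

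In Reliability: report same-day and different-day intrarater agreement separately. A higher same-day value should not be taken as proof of recall, since patients who fluctuate would be expected to agree better within a day anyway.

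The cost is a few sentences and sealed or locked sheets, with no extra staff, patients or assessments. The downside is that reasons for discrepancies are discussed up to a few days later, when they are less fresh, so examiners could note their reasons at the time of scoring. The examiner's own memory remains, and the intrarater result should be interpreted with that caution.

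### Examiners discuss their discrepancies right after the interrater session, which may be session 1 or 2, so examiner 1's later ratings of that patient are not independent

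*Protocol article*

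**What the plan says.** All of this is in the protocol article, mainly in the text below Figure 3 under Validation of the Study Procedure.

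- **Position of the interrater session.** "Directly before or after one of the three sessions, a second examiner will administer the SWADOC a second time to test its interrater reliability". The Figure 3 legend likewise names one of the three sessions and presents the programme as an example. Neither places this session last.
- **Blinding.** "The second assessment will be blinded to the results of the first".
- **Discussion.** Each scoring protocol is to be "analyzed directly after the interrater session and a discussion will follow to try to understand the reasons for any discrepancies". The reasons are then recorded.
- **Use of the sessions.** All three feed intrarater reliability, described as temporal stability. They also feed sensitivity to change, which relates variation in SECONDs to variation in the SWADOC-scored within a patient.
- **Use of the discussion's output.** Once recruitment is over and agreement has been analysed, "modifications of the instructions, and/or items will be considered based on the qualitative information collected from the examiners".
- **Analysis.** The Reliability section plans weighted Fleiss's kappa for intrarater and interrater agreement in two separate analyses. It does not distinguish ratings made before a discussion from those made after it.

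**The concern.** Blinding covers the second of the two paired ratings and nothing later. The joint discussion tells examiner 1 how a colleague scored this patient, and why. If sessions with that patient remain, examiner 1 rates again within the same five-day window with that knowledge. A comparison of ratings before and after then mixes three things: real change in the patient, the examiner's own consistency, and the effect of the discussion. Sensitivity to change suffers in the same way, because a scoring shift caused by the discussion appears as SWADOC change unrelated to consciousness.

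A second route runs through later patients. The Limitations section concedes that the ratings are subjective, and says of the planned analysis: "The interrater reliability will help us determine the consistency of the rating system between examiners". If examiners who have already debriefed together rate further patients, their agreement may reflect shared conventions as well as the written guide. Reliability is part of the main hypothesis, and revision of instructions or items depends on the agreement found. Raised agreement could therefore hide the ambiguities that the discussions are meant to reveal.

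**Working it through.** **The plan's own figures.** The article gives no figure for this point. Its one design calculation, 104 patients for a four-group ANOVA, reproduces: eta-squared 0.1 gives f = √(0.1/0.9) = 0.333, N = 103, or 104 with equal groups, with power 0.808 at 104. Neither the concern nor the fix affects it.

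**Which intrarater pairs are affected.** Both ratings of the interrater session precede the discussion. Examiner 1's three sessions form three pairs: 1–2, 1–3 and 2–3.

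- Interrater session is session 1: pairs 1–2 and 1–3 straddle the discussion (2 of 3).
- Session 2: pairs 1–3 and 2–3 straddle (2 of 3).
- Session 3: none straddle (0 of 3).

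The article does not say how often each position will be used. The affected share therefore lies between 0 and 2/3. If the three positions were used equally (an assumption), it would be (2 + 2 + 0)/9 = 4/9, about 44%.

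**How large the effect might be.** A simulation used 200,000 ratings of one four-level item. None of its inputs comes from the documents: latent trait SD 1, rating error SD 0.5, cut-points at −0.67, 0 and 0.67, quadratic weights, and a constant severity gap between the examiners. After the discussion both move towards the midpoint, closing none, half or all of the gap. The intrarater columns compare examiner 1 before and after.

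| Gap (SD) | Interrater: none closed | half | all | Intrarater: none closed | half | all |
|---|---|---|---|---|---|---|
| 0.3 | 0.694 | 0.717 | 0.724 | 0.726 | 0.723 | 0.715 |
| 0.6 | 0.614 | 0.695 | 0.725 | 0.722 | 0.716 | 0.694 |
| 1.0 | 0.467 | 0.646 | 0.722 | 0.718 | 0.699 | 0.642 |

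Interrater kappa in later patients rises by 0.03 (0.3 SD gap, all closed) to 0.26 (1.0 SD, all closed). On the article's own scale it stays in the substantial band (0.61 to 0.8) for gaps of 0.3 and 0.6 SD. At 1.0 SD it moves from moderate to substantial. Intrarater kappa in straddling pairs falls by 0.01 to 0.08 if the whole gap closes. The model has no term for recall of discussed scores, which would push intrarater agreement upwards.

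**A correlation model as cross-check.** Assume variance shares of 0.70 (patient), 0.15 (examiner-specific) and 0.15 (noise). After the discussion each examiner's deviation is a mix, with weight w on the other's.

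- Interrater r = [0.70 + 0.30w(1−w)] / [0.85 + 0.15((1−w)² + w²)]. This gives 0.70 at w = 0; 0.75625/0.94375 = 0.801 at w = 0.25; and 0.775/0.925 = 0.838 at w = 0.5.
- Intrarater r across the discussion = [0.70 + 0.15(1−w)] / √[0.85 + 0.15((1−w)² + w²)]. This gives 0.85, 0.836 and 0.806.

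The directions match the simulation. At w = 0.5 the two examiners' deviations are identical, so that row means complete convergence.

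**The case against.** Several points on the other side stand.

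- **Each patient's own interrater pair comes before its discussion.** Harm to interrater kappa can arise only by carry-over to later patients. The article does not give the number of examiners or say whether pairs are stable across its several hospitals and clinics.
- **Remaining sessions exist only if examiner 2 comes at session 1 or 2.** A reader might infer that every patient's later ratings are contaminated, and every later patient's too. The text does not support that.
- **No consensus score or agreed rule is described.** The stated purpose is to understand discrepancies, and changes to the tool wait until recruitment is over. Convergence is a plausible inference for subjective ratings, not a stated procedure.
- **The size is uncertain and may be small.** A reader might infer that debriefing lifts agreement from substantial to almost perfect. In the correlation model only 0.838 reaches that band, and it needs complete convergence; 0.801 does not reach it. That model also gives a correlation, not the planned kappa, and the kappa simulation shows no such crossing. The model's intrarater falls of 0.014 to 0.044 lie within sampling error: the standard error of r = 0.85 at N = 104 is about (1 − 0.85²)/√103 = 0.027, a 95% half-width of about 0.054.

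These points limit the claim but do not remove it. Sampling error does not excuse an avoidable bias, and nothing in the article stops examiner 1 from re-rating a patient whose scores have just been discussed.

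**Conclusion.** The concern holds in a limited form. As written, the plan lets a discussion of a patient's scores fall between examiner 1's ratings of that patient whenever the interrater session is the first or second. Intrarater and sensitivity-to-change comparisons that straddle it are not independent. This follows from the stated sequence alone. The share of session pairs affected is between 0 and 2/3, and 4/9 if positions are used equally. The direction of the intrarater bias is open.

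Inflation of interrater kappa in later patients is possible, but conditional on the same examiners continuing and on their readings converging. Its size depends wholly on the assumed gap: for 0.6 SD, from 0.61 to 0.70 with half the gap closed and to about 0.73 with all of it closed. The documents do not support a claim that the final agreement category will be wrong. The change is worth making because it is cheap and bears on the main reliability hypothesis.

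**What to change.** 1. Lock each score sheet at the end of its administration.
2. Have each examiner write the reasons for the ratings alone and immediately.
3. Hold the joint discussion no earlier than after that patient's third session, or make the interrater session the last one. Either protects the intrarater and sensitivity-to-change comparisons. Neither prevents carry-over to later patients.
4. For carry-over, either defer joint discussions to the end of data collection at the centre, or keep them after session 3 and report interrater weighted kappa by order of recruitment as a sensitivity analysis.

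Sample size and patient burden do not change. Reasons are discussed later, which the immediate notes largely offset, and little is lost because the output is used only after recruitment. Fixing the interrater session last costs some scheduling freedom. Deferral to the end at a centre means discussing old cases, since the Power section foresees recruitment to June 2025 or beyond. Reporting by recruitment order avoids that, but it can only reveal drift, not prevent it.
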